#### Secondary objectives

To track the trajectory of blood pressure (systolic, diastolic, and mean) within the study duration.To assess obstetric outcomes, including:Utilization of antihypertensive medication.Progression to severe preeclampsia or eclampsia.Incidence of pulmonary edema.Occurrence of fetal growth restriction.Presence of oligohydramnios.Occurrence of preterm placental abruption.Rate of preterm delivery (between 20 and 37 weeks).Incidence of miscarriage (before 20 weeks).Frequency of fetal demise.Evaluation of newborn weight.Assessment of low birth weight.Incidence of postpartum hemorrhage (including transfusion).

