### Eligibility criteria {10}

#### Inclusion criteria

Our prospective study plans to enroll 580 pregnant individuals who meet one of the following criteria for HDP [13].Chronic hypertension, defined as diagnosed hypertension within the first 20 weeks of gestation (elevated office or clinic blood pressure ≥ 140/90 mmHg) or ongoing antihypertensive medication usageGestational hypertension which involves pregnant individuals newly diagnosed with hypertension after the 20 weeks of gestation (elevated office or clinic blood pressure ≥ 140/90 mmHg) or those receiving antihypertensive treatment.Preeclampsia, characterized by new-onset hypertension after 20 weeks of gestation (elevated office or clinic blood pressure ≥ 140/90 mmHg) along with concurrent indicators such as proteinuria, thrombocytopenia, abnormal renal function, elevated liver enzymes, neurological symptoms, and pulmonary edema.Superimposed preeclampsia in pregnant individuals diagnosed with hypertension within 20 weeks of gestation or those on antihypertensive medication who experience symptoms or signs associated with this condition.Individuals with a heightened risk of pregnancy-related hypertension due to factors such as multiple pregnancies, obesity, diabetes, or a history of hypertension-related disorders in prior pregnancies leading to preterm birth.Prospective participants should be 18 years or older, possess a smartphone, be capable of using applications, and be proficient in the Korean language.

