### Intervention description {11a}

All study participants receive the standard care and continue to receive the same proactive treatment. They are provided with OMRON automatic blood pressure monitors and are instructed by the research nurse to measure their blood pressure once daily in a quiet environment; after a minimum of 5 min of rest, participants will undergo three consecutive blood pressure measurements, each taken at 5-min intervals. The mean of the second and third measurements is recorded. Based on the measured blood pressure, if necessary and at the discretion of the treating physician, adjustments or new prescriptions for antihypertensive medications will be made.

In the intervention group, participants also receive education from the research nurse on installing and navigating the Heart4U application. At the registration point and every 2 weeks thereafter, the usage and input levels of all participants will be monitored. Participants who log in less than three times in a 2-week period will be contacted to address any issues they might face with application usage. Furthermore, in the group using the Heart4U application, medical professionals will review the information recorded in the app through the integrated electronic medical records during antenatal visits. Both groups undergo observations in accordance with the antenatal examination schedule, and the clinical follow-up period will be 1 month after childbirth.

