#### Secondary outcomes

Trajectory blood pressure: Throughout the study duration, trajectories of systolic, diastolic, and mean blood pressure will be tracked.Obstetric outcomes: This includes but is not limited to:Antihypertensive medication useProgression to severe preeclampsia or eclampsiaPulmonary edemaFetal growth restrictionOligohydramniosPreterm placental abruptionPreterm delivery (between 20 and 37 weeks)Miscarriage (before 20 weeks)Fetal demiseNewborn weightLow birth weightPostpartum hemorrhage (including transfusion)Trajectory of body mass index (BMI): analysis of BMI trajectory.Physical activity monitoring: step counts recorded through Samsung Health or iPhone-Health applications.Depressive Mood Assessment: depressive symptoms will be assessed using surveys, including the Patient Health Questionnaires-9 and Beck Depression Inventory [15, 16], administered at enrollment and at the conclusion of the study. These tools are widely recognized and validated measures for evaluating depression symptoms and severity.Drug adherence: evaluation of medication adherence through pill counts

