## Statistical methods

### Statistical methods for primary and secondary outcomes {20a}

All continuous variables among the primary and secondary efficacy evaluation variables will be presented as mean and standard error or median and quartiles, and categorical variables will be summarized as percentages compared with the population parameters. Normally, two-sample *t*-tests or the Mann–Whitney *U* test, depending on whether the data follow a normal distribution, are used for continuous variables after assessing normality using the Kolmogorov–Smirnov test. The distributions of categorical variables are analyzed with *χ*^2^ tests or Fisher’s exact tests. The ITT principle will be used for all analyses. For each subgroup, we will calculate the hazard ratio and 95% confidence intervals for the primary and secondary endpoints. Statistical significance is set at a two-sided *P*-value of < 0.05. Statistical analyses will be performed using R version 4.3.1 (R Foundation for Statistical Computing, Vienna, Austria). The datasets analyzed in the current study will be available from the corresponding author upon request.

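### The tests named for secondary outcomes assume independent observations, so they do not fit BP and BMI trajectories, or newborn outcomes if siblings are counted separately

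*Protocol article*

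**What the plan says.** The section Statistical methods for primary and secondary outcomes {20a} covers primary and secondary variables together: "All continuous variables among the primary and secondary efficacy evaluation variables will be presented as mean and standard error or median and quartiles". It assigns continuous variables to a two-sample t-test or a Mann–Whitney U test, chosen after a normality test. For the others: "The distributions of categorical variables are analyzed with" chi-square or Fisher's exact tests. Sections {20b} and {20c} add analyses by app use, intention-to-treat and missing-data handling. No mixed model, GEE, cluster-robust variance or repeated-measures method is named anywhere in the article.

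Three other parts of the article bear on this:

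- **Who enters.** The Inclusion criteria admit "Individuals with a heightened risk of pregnancy-related hypertension due to factors such as multiple pregnancies, obesity, diabetes", among other routes.
- **What is compared.** The Secondary outcomes include newborn weight, low birth weight, fetal growth restriction and fetal demise. They also include BMI trajectory, and for BP: "Throughout the study duration, trajectories of systolic, diastolic, and mean blood pressure will be tracked".
- **How BP is collected.** Under Intervention description {11a}, women in both arms are "instructed by the research nurse to measure their blood pressure once daily in a quiet environment".

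**The concern.** A two-sample test takes one independent value per unit. Two groups of secondary outcomes do not arrive in that form.

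**Trajectories.** Each woman contributes many BP readings. Women may enter before or after 20 weeks of gestation and are followed to about one month after childbirth, so the length of the series and the number of readings differ between women. The article gives no rule for reducing a series to one number, and without such a rule the named tests have nothing valid to act on. This part of the point does not depend on twins.

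**Newborn outcomes.** Siblings share a mother and are always allocated together. If each infant is entered as a separate observation, the standard error is too small and the p-value too optimistic. If instead there is one value per mother, the tests are valid, but a rule is then needed for twins: for example, whether low birth weight means any infant or all infants, and whether newborn weight means the mean or the smallest.

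What is at stake is the credibility of the secondary comparisons. The article's Background and Discussion present better maternal and fetal outcomes as a main aim of the trial.

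**Working it through.** **1. The plan's own figure.** Inputs from Sample size {14}: difference 3.2 mmHg, SD 13 mmHg, two-sided alpha 0.05, power 80%.

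- n per arm = 2 × (1.960 + 0.842)² × 13² / 3.2² ≈ 259.1, rounded up to 260. The t-based solution is 260.04, rounded up to 261.
- 2 × 261 = 522, and 522 / 0.90 = 580.

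The stated 261, 522 and 580 reproduce. They concern one SBP change per woman, so clustering does not touch them.

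**2. Infants entered as separate observations.** Let f be the share of mothers with twins and r the within-pair correlation. The article gives neither, so both are assumptions. N mothers yield N(1 + f) infants. The variance of the sum is proportional to N(1 + f + 2fr), against N(1 + f) under independence. Hence:

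- design effect DE = 1 + 2fr / (1 + f)
- true type I error = 2 × [1 − Φ(1.96 / √DE)]
- naive SE as a fraction of the true SE = 1 / √DE

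Worked cases:

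- f = 20%, r = 0.5: DE = 1 + 0.20/1.20 = 1.167 and √DE = 1.080. The type I error is 0.070, and 1/1.080 = 0.926, so the naive SE is about 7% too small.
- f = 40%, r = 0.7: DE = 1 + 0.56/1.40 = 1.40 and √DE = 1.183. The type I error is 0.098, and 1/1.183 = 0.845, so the naive SE is about 15% too small.

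| Assumed twin share | Type I error, r = 0.3 | Type I error, r = 0.9 |
|---|---|---|
| 5% | 0.053 | 0.060 |
| 10% | 0.056 | 0.069 |
| 20% | 0.062 | 0.086 |
| 30% | 0.066 | 0.100 |
| 50% | 0.074 | 0.121 |

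**3. Simulation check.** 261 mothers per arm, r = 0.6, twin share 10% to 50%, 10,000 replicates per setting, run with and without a mean 1.2 SD lower in twins.

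- t-test on infants: type I error 0.059 to 0.101.
- t-test on one value per mother (twin mean): 0.046 to 0.053.

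The formula omits the difference in mean between twins and singletons. At a 10% twin share, adding it moved the simulated error from 0.059 to 0.077, so the low end of the table may be somewhat optimistic for birth weight.

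**4. BP readings pooled as if independent.** With m readings per woman and correlation r, DE = 1 + (m − 1)r. Both are assumptions.

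- m = 5: DE 2.2 to 3.8 for r = 0.3 to 0.7, type I error 0.19 to 0.32.
- m = 30: DE 9.7 to 21.3, type I error 0.53 to 0.67.

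These figures show what pooling would do. The article does not say that readings will be pooled.

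**The case against.** The strongest reply is that the article makes no such error. Pregnant women are recruited, randomised and counted, and newborn items are listed among obstetric outcomes beside maternal ones. One value per pregnancy is therefore a natural reading, and it keeps the type I error near 0.05. This stands. A reader might infer that the standard errors and p-values for these outcomes are wrong as planned. The documents do not support that, because they never say that infants or single readings are the unit of analysis.

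A second reply is that the unit and the trajectory model usually belong in the analysis plan, which is not shown, and that tracking a trajectory may be purely descriptive. This stands in part. Silence on the unit alone would not be a finding. But the methods section is not silent: it covers primary and secondary variables, and every test it names needs one independent value per unit. A summary per woman would make those tests usable, but none is given.

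A third reply concerns plurality. The only stratification factor named is medication adherence, and the tests are unadjusted, so a reader might infer that a chance imbalance in twins would bias the birth-weight comparison. It would not: it costs precision, and a valid test already allows for chance imbalance. Adjusting for plurality is worthwhile for precision only. Preterm delivery is a per-pregnancy outcome and has no sibling clustering.

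Finally, the inflation from twins is modest if few twin mothers enrol, and only secondary outcomes are affected. Both points stand.

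**Conclusion.** The stated methods do not fit some of the stated secondary outcomes, and the methods section should be changed. The trajectory part is the firmer one: the named tests cannot compare BP or BMI trajectories without first reducing each to one value per woman.

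The newborn part is conditional. If siblings are entered separately, a nominal 0.05 becomes about 0.053 to 0.12 over an assumed twin share of 5 to 50% and within-pair correlation of 0.3 to 0.9. With one predefined value per mother there is no inflation. The calculation covers twins only, not higher-order multiples.

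The primary endpoint, its test as regards clustering, and the 580 are unaffected. This should be corrected, but it does not threaten the trial's main result.

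**What to change.** Amend the section Statistical methods for primary and secondary outcomes {20a} as follows:

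- **Newborn and fetal outcomes** (newborn weight, low birth weight, growth restriction, fetal demise): state the unit for each. If it is the infant, use GEE or a mixed model with mother as the cluster and plurality as a covariate for precision, and report a mean difference or risk ratio with a 95% confidence interval. Otherwise define one value per mother, including the rule for multiples, and keep the simple tests.
- **BP and BMI trajectories:** use a linear mixed model for repeated measures with an arm-by-time term. Random intercept and slope, with time modelled separately before and after delivery, is one reasonable form. If the trajectories are meant to be descriptive only, say so.
- **Single per-mother outcomes:** keep the t, Mann–Whitney, chi-square and Fisher tests.

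The cost is statistical wording and routine programming, with slightly wider intervals for newborn outcomes analysed per infant. No extra participants or visits are needed. The change should be fixed before the outcome data are analysed by arm.

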### Sample size {14}

The determination of the sample size for this study, with an intended enrollment of 580 participants, was established using specific parameters as follows [17, 18]: the mean SBP at the point of enrollment was 146 mmHg, accompanied by a standard deviation of 13 mmHg. Subsequently, the mean SBP 1 month after childbirth was projected to be 130 mmHg, with a corresponding standard deviation of 12 mmHg. The control group displayed a delta SBP of 16 mmHg, whereas the delta SBP of the intervention group was amplified by 20% to 19.2 mmHg. The required difference between the two groups for sample size computation was 3.2. Moreover, a standard deviation of 13 mmHg was attributed to the delta SBP. These considerations are further coupled with an alpha error of 0.05 and a power of 80%. Using these variables, the calculations stipulated the necessity of 261 participants within each group, culminating in a total of 522. Considering a presumed dropout rate of 10%, the required comprehensive sample size was 580 participants.

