## Assignment of interventions: allocation

### Sequence generation {16a}

In this study, the allocation sequence was generated using SAS version 9.4 (SAS Institute, Cary, NC, USA) software. The allocation sequence was implemented and managed in the web-based case report form (CRF) system provided by GoodResearchUS (Seoul, Korea), where system roles and access permissions are established. Stratified permuted-block randomization was employed to ensure balanced assignment of subjects to each group. Block sizes were determined as multiples of 2 (e.g., 2, 4, 6). These blocks were generated using stratified randomization, with medication adherence as a stratification factor. Upon patient enrollment, the web-based CRF system generates a randomization table, automatically assigning participants to either the intervention or control group. This process is centrally managed, and allocation information is disclosed to participants immediately after group assignment.

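### Preterm delivery, newborn weight and related secondary outcomes are compared by unadjusted tests although multiple pregnancy is known at entry; the tests are valid, but some precision is given away.

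*Protocol article*

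**What the plan says.** All places are in the protocol article.

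- **Statistical methods {20a}.** Continuous primary and secondary variables get a two-sample t-test or Mann–Whitney test. "The distributions of categorical variables are analyzed with" chi-square or Fisher's exact tests. No covariate, stratified test or regression model is named for the comparison of arms.
- **Inclusion criteria {10}.** One entry route is raised risk of pregnancy-related hypertension due to "factors such as multiple pregnancies, obesity, diabetes" or an earlier hypertensive pregnancy that led to preterm birth.
- **Secondary outcomes {12}.** The list includes preterm delivery, newborn weight, low birth weight and fetal growth restriction.
- **Sequence generation {16a}.** Blocks are stratified "with medication adherence as a stratification factor". Plurality is not a stratum.
- **Additional analyses {20b} and non-adherence and missing data {20c}.** These deal with frequency of app use, compliance and imputation. Neither adds an adjusted comparison of the obstetric outcomes.

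**The concern.** Admitting women because they carry more than one fetus means that single and multiple pregnancies are pooled by design. Plurality can be expected to predict early delivery and low weight strongly. When it is ignored, the single-versus-multiple difference stays in the error term, and a chance imbalance between arms moves the estimate. The abstract and the discussion make better fetal outcomes an aim of the trial, and these secondary outcomes would carry that claim.

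The point is distinct from correlation between siblings. Preterm delivery occurs once per woman, so the loss applies to it even when its standard error is computed correctly.

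**Working it through.** **1. The plan's own figure.** From Sample size {14}: "The required difference between the two groups for sample size computation was 3.2", and "a standard deviation of 13 mmHg was attributed to the delta SBP". Alpha is 0.05 (two-sided per {20a}) and power 80%.

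- Normal approximation: n = 2 × (1.960 + 0.842)² × 13² / 3.2² = 259.1, so 260 per arm.
- With the t distribution, power is 79.99% at 260 and 80.15% at 261, so 261 per arm.
- 522 / 0.90 = 580.

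The stated size reproduces. It rests on change in systolic pressure alone; no power is claimed for obstetric outcomes.

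**2. Inputs for this point.** The document gives neither the share of multiples (w) nor outcome rates. All values below are assumptions, apart from 261 evaluable women per arm.

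**3. Preterm delivery (risk-difference scale).** With risk p0 in single and p1 in multiple pregnancies, and overall risk p = w·p1 + (1−w)·p0:

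explained share R² = w(1−w)(p1−p0)² / [p(1−p)]; ratio of standard errors = √(1−R²); unadjusted 95% half-width = 1.96 × √(2p(1−p)/261).

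| w | p0 v p1 | p(1−p) | R² | SE ratio | Half-width, points |
|---|---|---|---|---|---|
| 5% | 25% v 50% | 0.1936 | 1.5% | 0.992 | 7.55 → 7.49 |
| 10% | 25% v 50% | 0.1994 | 2.8% | 0.986 | 7.66 → 7.55 |
| 20% | 20% v 60% | 0.2016 | 12.7% | 0.934 | 7.70 → 7.20 |
| 30% | 15% v 60% | 0.2038 | 20.9% | 0.890 | 7.75 → 6.89 |

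The first and last rows are the extremes for w of 5–30%, p0 of 15–25% and p1 of 50–60%: R² about 2–21%, standard error about 1–11% smaller. If p0 may reach 30% and p1 70%, the extremes widen:

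- w = 5%, 30% v 50%: 0.0475 × 0.04 / 0.2139 = 0.9%.
- w = 30%, 15% v 70%: 0.21 × 0.3025 / 0.2158 = 29%, or a standard error 16% smaller.

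**4. Newborn weight.** With a gap of g within-group standard deviations, R² = w(1−w)g² / [1 + w(1−w)g²].

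- w = 5%, g = 0.8: 0.0304 / 1.0304 = 3.0% (standard error 1.5% smaller).
- w = 20%, g = 1.0: 0.16 / 1.16 = 13.8% (7% smaller).
- w = 30%, g = 1.5: 0.4725 / 1.4725 = 32% (18% smaller).

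These figures treat the outcome as one value per woman.

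**5. Chance imbalance.** At w = 20%, the 95% range of the between-arm difference in share of multiples is 1.96 × √(2 × 0.2 × 0.8 / 261) = ±6.9 points. With risks of 60% v 20% this moves the preterm difference by 0.40 × 6.86 = about ±2.7 points. The unadjusted interval already contains it: 7.20² + 2.75² = 59.4, and √59.4 = 7.7. Stratifying therefore saves about 0.5 points of half-width, not 2.7.

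**The case against.** The strongest reply is that nothing here is an error. Unadjusted tests are valid under randomisation, the outcomes are secondary, and no power is claimed for them. That stands in full. A reader might infer bias in the obstetric comparisons, or a consequence for the primary analysis or the sample size; the document supports neither. A reader might also take the ±2.7-point shift as error on top of the reported interval. It is part of that interval.

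Second, {20a} is a short journal paragraph, and covariates for secondary outcomes are often set in an analysis plan, which is not shown. This stands in part: the paragraph does not forbid supporting adjusted estimates. But it is not silent either. It names the tests for the secondary variables, and those tests are unadjusted.

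Third, the share of multiples may be small. Multiple pregnancy is one example in one of five entry routes, and Recruitment {15} speaks of women already diagnosed. This stands: at 5% multiples the gain is slight.

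Fourth, plurality is not the only baseline variable that could be used; entry diagnosis is another. That is fair, but it does not weaken the case for plurality, which can be expected to bear directly on gestation and weight.

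**Conclusion.** The point holds as a modest, optional gain in precision for preterm delivery, newborn weight, low birth weight and fetal growth restriction. It identifies neither an error nor a bias.

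That plurality is used in neither the design nor the named tests follows from the text. The size does not, because it rests wholly on assumed shares and rates. Under the main assumptions the standard error for preterm delivery would fall by about 1–11%, for example from a 95% half-width of 7.7 to 7.2 points at 20% multiples with risks of 60% v 20%. For newborn weight the fall would be about 1.5–18%. No size was worked out for low birth weight or growth restriction. If multiples make up 5% or less of enrolment, the benefit is small.

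**What to change.** In {20a}, add wording along these lines:

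- **Preterm delivery:** one record per woman; Mantel–Haenszel risk difference with 95% confidence interval, stratified by single versus multiple pregnancy at entry. The risk-difference scale matters: a covariate-adjusted logistic model can raise power but does not narrow the interval for the log odds ratio.
- **Newborn weight:** linear model with arm and plurality at entry.
- **Low birth weight and fetal growth restriction:** arm and plurality in the model, preferably reported as a risk difference.
- **Unit of analysis:** state for each of the last three outcomes whether it is the mother or the infant. If it is the infant, cluster standard errors by mother; a plain linear model at infant level would ignore sibling correlation.
- **Sparse outcomes:** keep the unadjusted exact test where strata are too thin.

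The cost is analysis wording, with no change to enrolment or procedures. Plurality at entry must be recorded for every woman, not only for those who qualify through it. The wording should be fixed before outcomes are compared by arm; Trial status gives August 2026 for the end of recruitment and June 2027 for completion.

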### Outcomes {12}

#### Primary outcome

The primary endpoint of this study is the difference in SBP measured between the point of enrollment and the conclusion of the study, which is 1 month ± 1 week after childbirth.

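### Subgroup results are specified as hazard ratios, but the primary endpoint and the continuous secondary endpoints have no event or event time, so a hazard ratio is undefined for them

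*Protocol article*

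**What the plan says.** The protocol article's section on statistical methods for primary and secondary outcomes {20a} fixes one effect measure for all subgroup results: "For each subgroup, we will calculate the hazard ratio and 95% confidence intervals for the primary and secondary endpoints". The sentence is not limited to event outcomes, and it names the primary endpoint expressly.

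The endpoint is defined under Primary outcome: "The primary endpoint of this study is the difference in SBP measured between the point of enrollment and the conclusion of the study", with the end of the study set at 1 month ± 1 week after childbirth. The primary objective {7} describes the same quantity.

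For the main comparison, section {20a} treats continuous endpoints as continuous: two-sample t-tests or the Mann–Whitney U test "are used for continuous variables after assessing normality using the Kolmogorov–Smirnov test". Categorical endpoints get chi-square tests "or Fisher’s exact tests".

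Under Secondary outcomes, several endpoints are measurements followed over time or taken once. For example, "trajectories of systolic, diastolic, and mean blood pressure will be tracked". BMI trajectory, newborn weight, step counts, depression questionnaire scores and pill counts are also listed. The remaining obstetric outcomes are mostly occurrences, such as preterm delivery or progression to severe preeclampsia.

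**The concern.** A hazard ratio compares the rates at which an event occurs over time in two groups. It needs an event, a time origin, a time to the event and a rule for censoring. A change in SBP between two visits supplies none of these. The subgroup analysis of the primary endpoint therefore cannot be carried out as stated, and the same is true of every continuous secondary endpoint.

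This is more than a detail left to the analysis plan, because the article positively names a measure that does not fit the endpoint. An analysis plan that follows the sentence inherits the error, and one that departs from it contradicts the published protocol. Either way someone must later choose another measure, and the sentence gives no guidance on which. In an open-label trial that choice is better made in writing before the data are analysed.

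**Working it through.** **1. How the primary endpoint is sized.** The inputs come from Sample size {14}:
- difference between groups: "The required difference between the two groups for sample size computation was 3.2" (mmHg, from 19.2 − 16);
- spread: "a standard deviation of 13 mmHg was attributed to the delta SBP";
- alpha 0.05 and power 80%, with two-sided testing from {20a} and 1:1 allocation from {8}.

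Normal approximation: n per group = 2 × (1.960 + 0.842)² × 13² / 3.2² = 2 × 7.849 × 169 / 10.24 ≈ 259.1, rounded up to 260. The t-test version gives 260.04, rounded up to 261, which is the article's figure. The total is 2 × 261 = 522, and 522 / (1 − 0.10) = 580, also as stated. Power at 261 per group is 0.803.

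The stated sample size therefore reproduces from a difference in means and a standard deviation. No number of events, event rate or hazard ratio enters it.

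**2. Endpoint by endpoint.** The subgroup sentence set beside the definitions and the main tests gives:
- *SBP change (primary):* continuous; main test t-test or Mann–Whitney U; no event or event time. Hazard ratio undefined.
- *Blood pressure and BMI trajectories, newborn weight, step counts, depression scores, pill counts:* measurements or counts; no event or event time. Hazard ratio undefined.
- *Obstetric occurrences (for example severe preeclampsia or eclampsia, pulmonary edema, preterm delivery, fetal demise):* categorical; main test chi-square or Fisher. A hazard ratio could be formed in principle, but the article defines no event time, censoring rule or survival model for any of them.

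The sections on withdrawal {11b}, additional analyses {20b} and missing data {20c} do not supply a time-to-event definition either.

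**3. What the subgroup estimate would look like on the trial's own scale.** For a mean difference with SD 13, the 95% CI half-width is 1.96 × 13 × √(2/m), where m is the number per arm in the subgroup:
- m = 261 (everyone): 2.2 mmHg;
- m = 130: 3.2 mmHg;
- m = 65: 4.5 mmHg.

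The sizes 130 and 65 are assumptions (about half and a quarter of the analysed sample), since the article gives no subgroup sizes. These figures show that a mean difference is directly available. They do not measure the size of the hazard-ratio error, which is simply that the quantity is undefined.

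**The case against.** The strongest reply is that the sentence governs subgroup reporting and nothing else. The main tests in {20a} suit the endpoint types, the sample size rests on a mean difference, and neither the primary conclusion nor its error rate depends on the subgroup measure. This stands, and it limits the weight of the point.

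It can also be said that the sentence is too sweeping rather than wholly wrong, because some obstetric occurrences could be analysed as time to event. This stands too, but only for those outcomes and only once event times and censoring are defined. It does not rescue the primary endpoint, which the sentence names.

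A reader might infer three stronger things that the document does not support.

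- *That the plan will judge subgroups against each other by their separate intervals, with no interaction test.* The article says that estimates and intervals will be calculated in each subgroup. It does not say that they will be compared in that way, and an interaction test is commonly left to the analysis plan. One can calculate that with two equal subgroups of 130.5 per arm and a true effect of 3.2 mmHg in both, the standardised effect is 3.2 / (13 × √(2/130.5)) = 1.99. Power in each is then about 0.51, and exactly one is significant with probability 2 × 0.51 × 0.49 ≈ 0.50. The arithmetic is right, but it assumes a split and a decision rule that the article does not state, and it says nothing about the hazard ratio.
- *That SBP would have to be dichotomised or recast as time to a threshold, at a cost in power.* Nothing in the article points there. The sample size and main tests already treat SBP change as continuous, so correcting the measure to a mean difference is at least as likely, and it loses nothing.
- *That the primary analysis itself is invalid.* It is not affected.

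**Conclusion.** The point holds in a limited form. The hazard ratio is undefined for the primary endpoint and for the continuous secondary endpoints. For the binary obstetric outcomes it lacks the definitions it would need and does not match the categorical tests assigned to them.

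The consequence is confined to subgroup reporting, with no effect on the main between-group comparison or on the 261 per group and 580 total. The conclusion rests on the endpoint definitions and tests as printed, and on the absence of any event-time or censoring definition in the article. An analysis plan that is not shown may already use suitable measures, but the published sentence would still be wrong. Severity: should fix.

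**What to change.** Replace the subgroup sentence in {20a} with one that ties the measure to the type of endpoint:
- for continuous endpoints, the between-group mean difference with 95% CI in each subgroup, in mmHg for SBP change;
- for binary obstetric endpoints, the risk ratio or risk difference with 95% CI in each subgroup, with one of the two chosen in advance;
- a hazard ratio only for an endpoint expressly defined as time to event, with its time origin and censoring stated.

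As optional supporting advice, a treatment-by-subgroup interaction term from a linear model (continuous endpoints) or a binary regression model (binary endpoints) would help readers interpret differences between subgroups. It is not needed to repair the sentence, and the primary test need not change.

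The cost is one sentence in the protocol, carried into the analysis plan before the data are analysed. No extra data, participants or visits are needed.
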